**5.3.8. Visit 04 (12 months  $\pm$ 30 days)**

- Review of continuing ability to consent/Advance Directive
- Review willingness to share contact information with FOUND or, if enrolled in FOUND, review individual status report
- PPMI Brain and Tissue Bank (for subjects who did not yet sign a form providing permission to be contacted by the Brain and Tissue Bank study team or have not yet signed an Intent to Donate form, review subject interest in PPMI Brain and Tissue Bank and remind interested subjects to follow up with the Brain and Tissue Bank study team or have subject sign an Intent to Donate form)
- General neurological examination
- Height and weight
- Vital signs (blood pressure, heart rate and temperature)

- Blood draw for research samples
- Urine collection for research samples
- Clinical laboratory assessments
- PASE Exercise Questionnaire
- Epworth Sleepiness Scale
- REM Sleep Behavior Disorder Questionnaire
- GDS-15
- State-Trait Anxiety Inventory
- Questionnaire for Impulsive-Compulsive Disorders
- SCOPA-AUT
- Montreal Cognitive Assessment (MoCA)
- Letter Number Sequencing
- Hopkins Verbal Learning Test – Revised (Form 2)
- Symbol Digit Modalities Test (Form 2)
- Benton Judgment of Line Orientation (Even items)
- Semantic Fluency
- Cognitive Categorization Assessment
- MDS-UPDRS Parts I-III (Part IV also conducted at each visit for subjects who have started PD medication)
- Hoehn and Yahr
- Modified Schwab & England (PD, Prodromal, SWEDD, and Genetic Cohort subjects only)
- MDS-UPDRS Part III and Hoehn & Yahr will be repeated one hour following dosing in clinic for subjects who have started levodopa or dopamine agonist
- Review of clinical diagnosis
- Review of family history of PD (Genetic Cohort subjects only)
- Lumbar puncture for collection of CSF
- SPECT imaging (PD and Prodromal subjects only – see Section 6.3.1), includes urine (or serum if required by site) pregnancy test for women of childbearing potential prior to injection
- VMAT-2 PET imaging, at selected sites, PD and Prodromal subjects (see Section 6.3.2)
- MRI-DTI and resting state (PD, Prodromal and HC subjects at selected sites)
- [F] florbetaben PET imaging at selected sites, PD (idiopathic and genetic cohorts), Prodromal (including RBD, olfactory and genetic cohort) subjects; or may be done at either V06 (24 months), V08 (36 months), V10 (48 months) or V12 (month 60); (or at V13 (month 72), V14 (month 84) or V15 (month 96) for PD and HC cohorts); see companion protocol.
- Gait assessments, at selected sites (Genetic Cohort subjects only) (see section 6.3.9 for details)
- Review of current medical conditions
- Review of concomitant medications
- Review of adverse events in follow up to SPECT (and/or VMAT-2 PET) imaging and/or lumbar puncture

- Consent/withdrawal of consent for contact regarding future studies related or unrelated to PPMI

Note Genetic Cohort will not undergo SPECT imaging, VMAT-2 imaging or DTI at Visit 04

**5.3.9. Visit 05 (18 months  $\pm$ 30 days)**

- Review of continuing ability to consent/Advance Directive
- Review willingness to share contact information with FOUND or, if enrolled in FOUND, review individual status report
- PPMI Brain and Tissue Bank (if subject has not yet been approached regarding Brain and Tissue Bank, review subject interest in sharing contact information with PPMI Brain and Tissue Bank study team or discuss Brain and Tissue Bank and present Intent to Donate form to subject)
- Vital signs (blood pressure, heart rate and temperature)
- Blood draws for research samples (including blood draw for PBMCs)
- MDS-UPDRS Parts I-III (PD, Prodromal SWEDD, and Genetic Cohort subjects only) (Part IV also conducted for subjects who have started PD medication)
- Hoehn and Yahr scale (PD, Prodromal, SWEDD and Genetic Cohort subjects only)
- Modified Schwab & England (PD, Prodromal, SWEDD and Genetic Cohort subjects only)
- Clinical diagnosis assessment (Prodromal, SWEDD and Genetic Cohort subjects only)
- Review of family history of PD (Genetic Cohort subjects only)
- Review of current medical conditions
- Review of concomitant medications
- Consent/withdrawal of consent for contact regarding future studies related or unrelated to PPMI

**5.3.10. Visit 06 (24 months  $\pm$ 30 days)**

- Review of continuing ability to consent/Advance Directive
- Review willingness to share contact information with FOUND or, if enrolled in FOUND, review individual status report
- PPMI Brain and Tissue Bank (for subjects who did not yet sign a form providing permission to be contacted by the Brain and Tissue Bank study team or have not yet signed an Intent to Donate form, review subject interest in PPMI Brain and Tissue Bank and remind interested subjects to follow up with the Brain and Tissue Bank study team or have subject sign an Intent to Donate form)
- General neurological examination
- Height and weight
- Vital signs (blood pressure, heart rate and temperature)
- Clinical laboratory assessments

- Blood draw for research samples
- Urine collection for research samples
- PASE Exercise Questionnaire
- Epworth Sleepiness Scale
- REM Sleep Behavior Disorder Questionnaire
- GDS-15
- State-Trait Anxiety Inventory
- Questionnaire for Impulsive-Compulsive Disorders
- SCOPA-AUT
- Montreal Cognitive Assessment (MoCA)
- Letter Number Sequencing
- Hopkins Verbal Learning Test – Revised (Form 3)
- Symbol Digit Modalities Test (Form 1)
- Benton Judgment of Line Orientation (Odd items)
- Semantic Fluency
- Cognitive Categorization Assessment
- MDS-UPDRS Parts I-III (Part IV also conducted at each visit for subjects who have started PD medication)
- Hoehn and Yahr
- Modified Schwab & England (PD, Prodromal, SWEDD and Genetic Cohort subjects only)
- MDS-UPDRS Part III and Hoehn & Yahr will be repeated one hour following dosing in clinic for subjects who have started levodopa or dopamine agonist
- Review of clinical diagnosis
- Review of family history of PD (Genetic Cohort subjects only)
- Lumbar puncture for collection of CSF
- SPECT imaging (PD, Prodromal, SWEDD, and Genetic Cohort subjects only – see Section 6.3.1), includes urine (or serum if required by site) pregnancy test for women of childbearing potential prior to injection
- VMAT-2 PET imaging, at selected sites, PD, SWEDD, Prodromal and Genetic Cohort subjects only (see Section 6.3.2)
- [F] florbetaben PET imaging at selected sites, PD (idiopathic and genetic cohorts), HC, and Prodromal (including RBD, olfactory and genetic cohort) subjects if not done at V04 (12 months); or may be done at V08 (36 months), V10 (48 months) or V12 (60 months); (or at V13 (month 72), V14 (month 84) or V15 (month 96) for PD and HC cohorts); see companion protocol.
- MRI DTI and resting state (PD, Prodromal, SWEDD and Genetic Cohort subjects at selected sites; HC at selected sites if not obtained at a previous visit)
- Gait assessments, at selected sites (Genetic Cohort subjects only) (see section 6.3.9 for details)
- Review of current medical conditions
- Review of concomitant medications
- Review of adverse events in follow up to SPECT (and/or VMAT-2 PET) imaging and/or lumbar puncture

- Consent/withdrawal of consent for contact regarding future studies related or unrelated to PPMI
- Conclusion of study participation (SWEDD subjects only, unless continuing participation). Note SWEDD subjects may be asked to continue follow up through up to V15/Month 96 at the investigator's discretion, if by clinical assessment (e.g., subject had a positive scan at or before Month 24), the investigator determines there is substantial evidence that the subject may have PD.

**5.3.11. Visit 07 (30 months  $\pm$ 30 days)**

- Review of continuing ability to consent/Advance Directive
- Review willingness to share contact information with FOUND or, if enrolled in FOUND, review individual status report
- PPMI Brain and Tissue Bank (if subject has not yet been approached regarding Brain and Tissue Bank, review subject interest in sharing contact information with PPMI Brain and Tissue Bank study team or discuss Brain and Tissue Bank and present Intent to Donate form to subject)
- Reconsent (For SWEDDS returning to the study)
- Vital signs (blood pressure, heart rate and temperature)
- Blood draws for research samples (including blood draw for PBMCs)
- MDS-UPDRS Parts I-III (PD, Prodromal and Genetic Cohort subjects only) (Part IV also conducted at each visit for subjects who have started PD medication)
- Hoehn and Yahr scale (PD, Prodromal and Genetic Cohort subjects only)
- Modified Schwab & England (PD, Prodromal and Genetic Cohort subjects only)
- Clinical diagnosis assessment (Prodromal and Genetic Cohort subjects only)
- Review of family history of PD (Genetic Cohort subjects only)
- Review of current medical conditions
- Review of concomitant medications
- Consent/withdrawal of consent for contact regarding future studies related or unrelated to PPMI

**5.3.12. Visit 08 (36 months  $\pm$ 30 days)**

- Review of continuing ability to consent/Advance Directive
- Review willingness to share contact information with FOUND or, if enrolled in FOUND, review individual status report
- PPMI Brain and Tissue Bank (for subjects who did not yet sign a form providing permission to be contacted by the Brain and Tissue Bank study team or have not yet signed an Intent to Donate form, review subject interest in PPMI Brain and Tissue Bank and remind interested subjects to follow up with the Brain and Tissue Bank study team or have subject sign an Intent to Donate form)
- General neurological examination

- Height and weight
- Vital signs (blood pressure, heart rate and temperature)
- Clinical laboratory assessments
- Blood draw for research samples
- Urine collection for research samples
- PASE Exercise Questionnaire
- Epworth Sleepiness Scale
- REM Sleep Behavior Disorder Questionnaire
- GDS-15
- State-Trait Anxiety Inventory
- Questionnaire for Impulsive-Compulsive Disorders
- SCOPA-AUT
- Montreal Cognitive Assessment (MoCA)
- Letter Number Sequencing
- Hopkins Verbal Learning Test – Revised (Form 4)
- Symbol Digit Modalities Test (Form 2)
- Benton Judgment of Line Orientation (Even items)
- Semantic Fluency
- Cognitive Categorization Assessment
- UPSIT (Prodromal and Unaffected Genetic Cohort subjects only; if subject has already completed their month 36 visit at time of amendment 12 approval, this may be completed at a later visit)
- MDS-UPDRS Parts I-III (Part IV also conducted at each visit for subjects who have started PD medication)
- Hoehn and Yahr
- Modified Schwab & England (PD, Prodromal, and Genetic Cohort subjects only)
- MDS-UPDRS Part III and Hoehn & Yahr will be repeated one hour following dosing in clinic for subjects who have started levodopa or dopamine agonist
- SPECT imaging (Prodromal subjects only), includes urine (or serum if required by site) pregnancy test for women of childbearing potential prior to injection
- [F] florbetaben PET imaging at selected sites, PD (idiopathic and genetic cohorts), HC, and Prodromal (including RBD, olfactory and genetic cohort) subjects if not done at V04 or V06; or may be done at V10 (48 months) or V12 (60 months); (or at V13 (month 72), V4 (month 84) or V15 (month 96) for PD and HC cohorts); see companion protocol.
- MRI-DTI and resting state, HC at selected sites if not obtained at a previous visit
- Gait assessments, at selected sites (Genetic Cohort subjects only) (see section 6.3.9 for details)
- Review of clinical diagnosis
- Review of family history of PD (Genetic Cohort subjects only)
- Lumbar puncture for collection of CSF
- Review of current medical conditions
- Review of concomitant medications

- Review of adverse events related to SPECT imaging and/or lumbar puncture
- Consent/withdrawal of consent for contact regarding future studies related or unrelated to PPMI

**5.3.13. Visit 09 (42 months  $\pm$ 30 days)**

- Review of continuing ability to consent/Advance Directive
- Review willingness to share contact information with FOUND or, if enrolled in FOUND, review individual status report
- PPMI Brain and Tissue Bank (if subject has not yet been approached regarding Brain and Tissue Bank, review subject interest in sharing contact information with PPMI Brain and Tissue Bank study team or discuss Brain and Tissue Bank and present Intent to Donate form to subject)
- Vital signs (blood pressure, heart rate and temperature)
- Blood draws for research samples (including blood draw for PBMCs)
- MDS-UPDRS Parts I-III (PD, Prodromal, and Genetic Cohort subjects only) (Part IV also conducted at each visit for subjects who have started PD medication)
- Hoehn and Yahr scale (PD, Prodromal, and Genetic Cohort subjects only)
- Modified Schwab & England (PD, Prodromal, and Genetic Cohort subjects only)
- Clinical diagnosis assessment (Prodromal, and Genetic Cohort subjects only)
- Review of family history of PD (Genetic Cohort subjects only)
- Review of current medical conditions
- Review of concomitant medications
- Consent/withdrawal of consent for contact regarding future studies related or unrelated to PPMI

**5.3.14. Visit 10 (48 months  $\pm$ 30 days)**

- Review of continuing ability to consent/Advance Directive
- Review willingness to share contact information with FOUND or, if enrolled in FOUND, review individual status report
- PPMI Brain and Tissue Bank (for subjects who did not yet sign a form providing permission to be contacted by the Brain and Tissue Bank study team or have not yet signed an Intent to Donate form, review subject interest in PPMI Brain and Tissue Bank and remind interested subjects to follow up with the Brain and Tissue Bank study team or have subject sign an Intent to Donate form)
- General neurological examination
- Height and weight
- Vital signs (blood pressure, heart rate and temperature)
- Clinical laboratory assessments
- Blood draw for research samples
- Urine collection for research samples
- PASE Exercise Questionnaire

- Epworth Sleepiness Scale
- REM Sleep Behavior Disorder Questionnaire
- GDS-15
- State-Trait Anxiety Inventory
- Questionnaire for Impulsive-Compulsive Disorders
- SCOPA-AUT
- Montreal Cognitive Assessment (MoCA)
- Letter Number Sequencing
- Hopkins Verbal Learning Test – Revised (Form 5)
- Symbol Digit Modalities Test (Form 1)
- Benton Judgment of Line Orientation (Odd items)
- Semantic Fluency
- Cognitive Categorization Assessment
- MDS-UPDRS Parts I-III (Part IV also conducted at each visit for subjects who have started PD medication)
- Hoehn and Yahr
- Modified Schwab & England (PD, Prodromal, and Genetic Cohort subjects only)
- MDS-UPDRS Part III and Hoehn & Yahr will be repeated one hour following dosing in clinic for subjects who have started levodopa or dopamine agonist
- Review of clinical diagnosis
- Review of family history of PD (Genetic Cohort subjects only)
- Lumbar puncture for collection of CSF
- SPECT imaging (PD, prodromal and Genetic Cohort subjects only – see Section 6.3.1), includes urine (or serum if required by site) pregnancy test for women of childbearing potential prior to injection
- VMAT-2 PET imaging, at selected sites, PD, and Genetic Cohort subjects only (see Section 6.3.2)
- MRI DTI and resting state (PD, and Genetic Cohort subjects at selected sites; HC at selected sites if resting state sequences were not obtained at a previous visit)
- [F] florbetaben PET imaging at selected sites, PD (idiopathic and genetic cohorts), HC, and Prodromal (including RBD, olfactory and genetic cohort) subjects if not done at V04, V06 or V08; or may be done at V12 (60 months); (or at V13 (month 72), V14 (month 84) or V15 (month 96) for PD and HC cohorts); see companion protocol.
- Gait assessments, at selected sites (Genetic Cohort subjects only) (see section 6.3.9 for details)
- Review of current medical conditions
- Review of concomitant medications
- Review of adverse events in follow up to SPECT imaging (and/or VMAT-2 PET) and/or lumbar puncture
- Consent/withdrawal of consent for contact regarding future studies related or unrelated to PPMI

**5.3.15. Visit 11 (54 months  $\pm$ 30 days)**

- Review of continuing ability to consent/Advance Directive
- Review willingness to share contact information with FOUND or, if enrolled in FOUND, review individual status report
- PPMI Brain and Tissue Bank (if subject has not yet been approached regarding Brain and Tissue Bank, review subject interest in sharing contact information with PPMI Brain and Tissue Bank study team or discuss Brain and Tissue Bank and present Intent to Donate form to subject)
- Vital signs (blood pressure, heart rate and temperature)
- Blood draws for research samples (including blood draw for PBMCs)
- MDS-UPDRS Parts I-III (PD and Genetic Cohort subjects only) (Part IV also conducted at each visit for subjects who have started PD medication)
- Hoehn and Yahr scale (PD and Genetic Cohort subjects only)
- Modified Schwab & England (PD and Genetic Cohort subjects only)
- Clinical diagnosis assessment (Genetic Cohort subjects only)
- Review of family history of PD (Genetic Cohort subjects only)
- Review of current medical conditions
- Review of concomitant medications
- Consent/withdrawal of consent for contact regarding future studies related or unrelated to PPMI

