| MDS-UPDRS (including Hoehn & Yahr) h                                                                                       |                   |         | X        | X              | X   | X              | X   | X                | X                | X                | X                | X                 | X                | X                | X   | X              | X               | X              |                |
| Modified Schwab & England ADL                                                                                                         |                   |         | X        | X              | X   | X              | X   | X                | X                | X                | X                | X                 | X                | X                | X   | X              | X               | X              |                |
| MDS-UPDRS Repeat Part III/Hoehn & Yahr j                                                                                   |                   |         |          |                |     |                |     | X                |                  | X                |                  | X                 |                  | X                |     |                | X               |                |                |
| Clinical Diagnosis Assessments                                                                                                        |                   |         | X        | X              | X   | X              | X   | X                | X                | X                | X                | X                 | X                | X                |     |                | X               | X              |                |
| Physical Activity Scale for the Elderly (PASE)                                                                                        |                   |         |          | X              |     |                |     | X                |                  | X                |                  | X                 |                  | X                |     | X              | X               |                |                |

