| Biomic blood sample                                                                                                                 |                   |          | X f | X f | X f   | X                | X f   | X                | X f   | X                | X f   | X                | X f | *X f |                |
| PBMC blood sample                                                                                                                   |                   |          | X              | X              |                  | X                |                  | X                |                  | X                |                  | X                |                |                 |                |
| MDS-UPDRS (including Hoehn & Yahr) h                                                                                     |                   | X        | X              | X              | X                | X                | X                | X                | X                | X                | X                | X                | X              | X               |                |
| Modified Schwab & England ADL                                                                                                       |                   | X        | X              | X              | X                | X                | X                | X                | X                | X                | X                | X                | X              | X               |                |
| Clinical Diagnosis Assessment(s)                                                                                                    |                   | X        |                | X              | X                | X                | X                | X                | X                | X                | X                | X                | X              | X               |                |
| MDS-UPDRS Repeat Part III/Hoehn & Yahr j                                                                                 |                   |          | X              |                | X                |                  | X                |                  | X                |                  | X                |                  | X              | X               |                |

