### **2.2. Secondary Objectives**

- 2.2.1. To evaluate the probability of a change over a 24-month period in the clinical diagnosis of PPMI PD subjects with a baseline dopamine transporter image that shows no evidence for striatal DAT or VMAT deficit (SWEDD).
- 2.2.2. Assess the influence of dopamine transporter or VMAT2 imaging status on the clinical diagnosis and management of SWEDD subjects.
- 2.2.3. To evaluate the probability of phenoconversion to PD for individuals enrolled in the Prodromal cohort and Unaffected Genetic Cohort.
- 2.2.4. Investigate existing and identify novel clinical, imaging, and biomic Parkinson disease progression markers to identify quantitative individual measures or combination of measures that demonstrate optimum interval change of SWEDD subjects in comparison to healthy controls, PD subjects, Prodromal subjects, Genetic Cohort or in sub-sets of PD patients defined by baseline assessments, genetic mutations, progression milestones and/or rate of clinical, imaging, or biomic change.

- 2.2.5. Investigate existing and identify novel clinical, imaging, and biomic Parkinson disease progression markers to identify quantitative individual measures or combination of measures that demonstrate optimum interval change of Prodromal subjects (including both prodromal cohort and Unaffected Genetic Cohort) in comparison to healthy controls, PD subjects, SWEDD subjects or sub-sets of PD patients defined by baseline assessments, progression milestones and/or rate of clinical, imaging, or biomic change.

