**5.3.16. Visit 12 (60 months  $\pm$ 30 days)**

- Review of continuing ability to consent/Advance Directive
- Review willingness to share contact information with FOUND or, if enrolled in FOUND, review individual status report
- PPMI Brain and Tissue Bank (for subjects who did not yet sign a form providing permission to be contacted by the Brain and Tissue Bank study team or have not yet signed an Intent to Donate form, review subject interest in PPMI Brain and Tissue Bank and remind interested subjects to follow up with the Brain and Tissue Bank study team or have subject sign an Intent to Donate form)
- General neurological examination
- Height and weight
- Vital signs (blood pressure, heart rate and temperature)
- Clinical laboratory assessments
- Blood draw for research samples
- Urine collection for research samples
- PASE Exercise Questionnaire
- Epworth Sleepiness Scale
- REM Sleep Behavior Disorder Questionnaire
- GDS-15
- State-Trait Anxiety Inventory
- Questionnaire for Impulsive-Compulsive Disorders
- SCOPA-AUT

- Montreal Cognitive Assessment (MoCA)
- Letter Number Sequencing
- Hopkins Verbal Learning Test – Revised (Form 6)
- Symbol Digit Modalities Test (Form 2)
- Benton Judgment of Line Orientation (Even items)
- Semantic Fluency
- Cognitive Categorization Assessment
- MDS-UPDRS Parts I-III (Part IV also conducted at each visit for subjects who have started PD medication)
- Hoehn and Yahr
- Modified Schwab & England (PD, prodromal, PD and Unaffected Genetic Cohort subjects only)
- MDS-UPDRS Part III and Hoehn & Yahr will be repeated one hour following dosing in clinic for subjects who have started levodopa or dopamine agonist
- Review of clinical diagnosis
- Review of family history of PD (Genetic Cohort subjects only)
- Lumbar puncture for collection of CSF
- MRI DTI and resting state (PD and Genetic Cohort subjects at selected sites; HC at selected sites if resting state sequences were not obtained at a previous visit).
- [F] florbetaben PET imaging at selected sites, PD (idiopathic and genetic cohorts), HC and Prodromal (genetic cohort) subjects if not done at V04 or V06 or V10; (or may be done at V13 (month 72), V14 (month 84) or V15 (month 96) for PD and HC cohorts); see companion protocol.
- Gait assessments, at selected sites (Genetic Cohort subjects only) (see section 6.3.9 for details)
- Review of current medical conditions
- Review of concomitant medications
- Review of adverse events related to lumbar puncture

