#### **6.1.6. Diagnostic Questionnaire**

The Diagnostic Questionnaire is being used for the Prodromal and Genetic Cohort and Registry subjects to allow Investigators to provide a detailed assessment regarding any clinical signs and symptoms and to document any changes in diagnosis. This assessment and the Diagnostic Features assessment will be used as research based criteria for determining phenoconversion to motor PD as assessed by the Investigator.

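### Prodromal subjects have no research diagnosis assessment at Month 54, and schedule and visit text conflict at Months 54 and 60, so Year-5 phenoconversion is ascertained less often than in the Unaffected Genetic Cohort

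*Protocol*

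**What the plan says.** Objective 2.2.3 is "To evaluate the probability of phenoconversion to PD for individuals enrolled in the Prodromal cohort and Unaffected Genetic Cohort", with no time limit. Section 6.1.6 says that the Diagnostic Questionnaire, together with the Diagnostic Features assessment, "will be used as research based criteria for determining phenoconversion to motor PD as assessed by the Investigator". The scheduled diagnosis assessment is therefore the endpoint measurement.

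- **Prodromal schedule.** The row "Clinical Diagnosis Assessments" is marked at Screening, Baseline and every visit from V01 to V10 (Month 48). It is blank at V11 (Month 54) and V12 (Month 60), and marked again for premature withdrawal and symptomatic therapy.
- **Month 42 text (5.3.13).** "Clinical diagnosis assessment (Prodromal, and Genetic Cohort subjects only", so Prodromal subjects are included at the preceding interim visit.
- **Month 54 text (5.3.15).** "Clinical diagnosis assessment (Genetic Cohort subjects only". The motor rating line reads "MDS-UPDRS Parts I-III (PD and Genetic Cohort subjects only", and the Hoehn and Yahr and Modified Schwab & England lines carry the same limit.
- **Month 60 text (5.3.16).** "Review of clinical diagnosis" stands without a cohort limit. So does the repeat of Part III and Hoehn and Yahr for those on levodopa or a dopamine agonist.
- **Unaffected Genetic Cohort schedule.** The row "Clinical Diagnosis Assessment(s" is marked at both V11 and V12.

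**The concern.** The Prodromal cohort was recruited because it is at high risk of converting, and its diagnosis assessment stops after Month 48 while the other at-risk cohort keeps its own every six months to Month 60. Because that assessment defines the endpoint, a visit without it leaves conversion status unmeasured by the protocol's own criteria. A conversion in this window is dated later, or depends on someone outside the research visit making the diagnosis. Sites also face two pairs of instructions that cannot both be followed. Section 4.1 gives Prodromal follow-up as 5 to 10 years. A subject who completes at Month 60, at a site that follows the schedule, has no scheduled research diagnosis after Month 48.

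**Working it through.** No sample size or power figure bears on this point. The one related figure is in 14.5: 30% conversion over 24 months in about 100 subjects, with a 95% interval of about ±10%. It recomputes as 1.96 × √(0.3 × 0.7 / 100) = 0.090, consistent with the statement, and it concerns a period before the gap.

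The check is a cell-by-cell reading of the schedules against their visit headers (Prodromal 19 cells to 19 headers, Unaffected Genetic 15 to 15), set beside the visit text.

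**Diagnosis assessment**

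| Visit | Prodromal, schedule | Prodromal, visit text | Unaffected Genetic, schedule |
|---|---|---|---|
| V10, Month 48 | marked | listed for all | marked |
| V11, Month 54 | blank | not listed | marked |
| V12, Month 60 | blank | listed for all | marked |
| V13, Month 72 | marked | listed for all | marked |

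**Other rows, Prodromal**

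| Item | Schedule | Visit text |
|---|---|---|
| MDS-UPDRS with Hoehn and Yahr, V11 | marked | PD and Genetic Cohort only |
| Modified Schwab & England, V11 | marked | PD and Genetic Cohort only |
| Repeat Part III / Hoehn and Yahr, V12 | blank | all on levodopa or agonist |

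**Scheduled diagnosis assessments after Month 48 and up to Month 60**

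- Unaffected Genetic: 2 (Months 54 and 60).
- Prodromal: 0 by the schedule, 1 by the text.

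**Interval from Month 48 to the next scheduled assessment**

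- Prodromal, by the text: 60 − 48 = 12 months.
- Prodromal, by the schedule: 72 − 48 = 24 months.
- Unaffected Genetic: 54 − 48 = 6, then 60 − 54 = 6, then 72 − 60 = 12 months.

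**Other routes to a diagnosis in the window**

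- The phenoconversion visit (5.3.27) follows a diagnosis already made in clinical care.
- The symptomatic therapy visit (5.3.24, 5.3.26) includes a diagnosis assessment, but needs PD medication to be starting and the subject to agree.
- The premature withdrawal visit (5.3.23) includes one, but only for those who leave early and agree to it.
- A change of diagnosis is a reportable event (Section 11, Reportable Events), but it must first be known.
- The calls at Months 51 and 57 deal with questions, medication starts and the next visit date (5.3.21).

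Each of these needs something to have happened or been noticed first. None is a systematic assessment of an untreated subject without a diagnosis.

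**The case against.** The best reply is that the visit text governs. Section 5.2 describes the schedule as a summary, and 5.3 says that subjects undergo the procedures in the visit sections. On that reading Month 60 is covered for everyone, the blank cell is a slip, and the gap is 12 months. That is fair, and it is why Month 60 is put here as a conflict to reconcile and not as a settled omission. But the same reading removes MDS-UPDRS, Hoehn and Yahr and Schwab & England from Prodromal subjects at Month 54, and it leaves the missing diagnosis assessment there in place.

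It can also be said that no planned analysis is damaged. The stated phenoconversion percentages are at two years (3.2(e), 14.3.4, 14.4.6), and 14.4.7 is a logistic model, not a time-to-event one. Section 14.5 mentions only exploratory comparisons of the Prodromal and Unaffected Genetic cohorts. Assessment was never identical either: Prodromal subjects are assessed at Months 3 and 9, when the Genetic Cohort has no visit. All of this stands. It confines the consequence to objective 2.2.3, which has no two-year limit, and to descriptive comparison of the cohorts in that window.

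The event-triggered routes are real partial cover, and the Month 60 neurological examination and MDS-UPDRS may bring a change of diagnosis to light. They reduce the loss but do not equalise ascertainment.

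**Conclusion.** The point holds in a limited form. Prodromal subjects have no research diagnosis assessment at Month 54 by either source. At Month 60 the schedule and the text disagree about the diagnosis assessment and the repeat Part III, and at Month 54 they disagree about the motor and function ratings. Conversions between Months 48 and 60, or up to Month 72 if the schedule is followed, are therefore ascertained less often than in the Unaffected Genetic Cohort: a gap of 12 or 24 months, against 6-monthly assessment to Month 60. The 24-month figure takes the modified schedule's columns as they stand, with Month 72 first and no call at Month 66.

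Three stronger readings are tempting but unsupported.

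- A reader might infer that phenoconversion goes unascertained for good after Month 48. It does not: from Month 72 one schedule serves both cohorts, with diagnosis at every annual visit and six-monthly call.
- A reader might infer that the two-year conversion estimate is biased. Every Prodromal visit to Month 48 has the assessment, so it is untouched.
- A reader might infer a count of lost conversions. With an assumed 70 subjects unconverted at Month 48 and an assumed yearly hazard of 5% to 15%, 70 × (1 − e^−0.05) = 3.4 and 70 × (1 − e^−0.15) = 9.8. The protocol gives neither input, and the sum counts every Year-5 conversion as affected. By the visit text, those arising in Months 54 to 60 are assessed at Month 60, as in the other cohort. No count should be reported.

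This is a consistency correction worth making because the endpoint assessment is otherwise skipped at a visit that takes place anyway.

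**What to change.** In the Prodromal Schedule of Activities, mark the clinical diagnosis row at V11 and V12, and mark the repeat Part III/Hoehn & Yahr row at V12 to agree with 5.3.16. In 5.3.15, add Prodromal to the clinical diagnosis, MDS-UPDRS, Hoehn and Yahr and Modified Schwab & England lines. This brings the text into line with the motor and function marks already in the Prodromal schedule, and matches the Unaffected Genetic Cohort's diagnosis assessments at Months 54 and 60.

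The cost is amendment wording for three table cells and four text lines, and a few minutes of investigator time at two existing visits with a form already used at earlier ones. If Prodromal subjects have already passed these visits under the present wording, an analysis of Year-5 conversion should treat their conversion times as interval-censored between the assessments actually done.
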